## Study Synopsis

|                                                |                                                                                                                                                                                                                                                                                                              |
|------------------------------------------------|--------------------------------------------------------------------------------------------------------------------------------------------------------------------------------------------------------------------------------------------------------------------------------------------------------------|
| Title of clinical trial                        | A multi-centre randomised controlled trial to compare three treatments; cervical cerclage, cervical pessary and vaginal progesterone                                                                                                                                                                         |
| Short Title/Acronym                            | SuPPORT: Stitch, Progesterone or Pessary: a Randomised Trial                                                                                                                                                                                                                                                 |
| Chief Investigator                             | [name]
Women's Health Academic Centre
Kings College [name]
[contact]                                                                                                                                                                                     |
| Medical condition under investigation          | Short cervical length and spontaneous preterm birth                                                                                                                                                                                                                                                          |
| Purpose of clinical trial                      | This trial will evaluate whether a cervical cerclage, cervical pessary or vaginal progesterone are equally efficacious to prevent spontaneous premature birth for women at high-risk of spontaneous preterm birth who develop a short cervix between 14 +0 and 23 +6 weeks' gestation. |
| Trial Design                                   | Multicentre Randomised controlled trial                                                                                                                                                                                                                                                                      |
| Primary Endpoint                               | Preterm birth rate < 37 weeks gestation                                                                                                                                                                                                                                                                      |
| Sample size                                    | 540                                                                                                                                                                                                                                                                                                          |
| Summary of eligibility criteria                | Women with singleton pregnancies at high risk of preterm birth who are found to have cervical length <25 mm on transvaginal ultrasound between 14 +0 weeks' until 23 +6 weeks' gestation                                                                                               |
| Investigational medicinal products             | Cervical cerclage vs Progesterone 200 mg PV, vs Arabin cervical pessary                                                                                                                                                                                                                                      |
| Maximum duration of treatment of a participant | 28 weeks                                                                                                                                                                                                                                                                                                     |

[figure not shown]

Trial Flowchart

[figure not shown]

[figure not shown]

## Professional Summary

Preterm birth, defined as birth before 37 weeks' completed gestation, is a major challenge facing modern obstetrics, with a global prevalence of 9.6% and over a million annual neonatal deaths. The authors of the 2012 WHO report 'Born Too Soon: The Global Action Report on Preterm Birth, highlighted the unacceptably high and seemingly irretractable rate of prematurity worldwide, and emphasised the importance of continued research into biomarker strategies to predict women at risk and target clinical management appropriately as well as research into optimal interventions to reduce the risk of preterm birth.

In clinical practice, once a woman has been identified as being at risk of spontaneous preterm birth (sPTB), as defined by a short cervical length (<25 mm) on transvaginal ultrasound scan, a decision regarding prophylactic treatment must be made. There are three interventions with the potential to improve outcome in these high-risk women prior to 24 weeks' gestation: cervical cerclage (stitch), vaginal progesterone treatment and cervical pessary. Each have been shown to have similar benefit in reduction of sPTB in women who develop a short cervix, but there have been *no* randomised control trials (RCTs) to compare the efficacy of each intervention; decision for intervention is currently based upon clinician experience and patient preference. This trial will evaluate whether a cervical cerclage, cervical pessary or vaginal progesterone are equally efficacious to prevent premature birth for women at high-risk of preterm birth who develop a short cervix (<25 mm) between 14+0 and 23+6 weeks' gestation as measured by transvaginal ultrasonography.

It will evaluate the impact of the three interventions on:

1. Obstetric outcome –premature birth rate <37 weeks' of gestation (primary), 34 weeks and 30 weeks (secondary outcomes).
2. Short-term neonatal outcomes –a composite of death and major morbidity

It will also explore whether success of the intervention can be predicted by pre-intervention biomarker and status (cervicovaginal fluid, blood and saliva).

Participants will be women with singleton pregnancies identified as high risk of sPTB (i.e. either a history of sPTB, second trimester loss, premature pre-labour fetal membrane rupture, previous cervical surgery or incidental findings of a short cervix) will be screened from 14 weeks' gestation with transvaginal ultrasonography. Asymptomatic women who develop a short cervix (<25 mm) will be randomised to either a cervical pessary (arabin), cervical cerclage or vaginal progesterone 200 mg once daily.

The trial is a UK multi-centre open label randomised controlled trial. The results of this study will be used to develop evidencebased local and national guidelines to better inform clinical practice.

[figure not shown]

## 1 INTRODUCTION

### 1.1 Background

There are 12.9 million premature births annually worldwide and despite the magnitude of the problem, there is no established early pregnancy screening test or effective treatment for women once a high risk of spontaneous preterm birth (sPTB) is ascertained. The associated morbidity, mortality and high health costs are well documented. Only 39% of those infants born <26 weeks' gestation survive and 13% of these suffer severe cerebral palsy or sensory impairment. Despite considerable efforts to introduce new therapies for the prevention and treatment of spontaneous preterm labour, sPTB rates are still rising; 6% of births in the UK are premature. sPTB is thought to be the result of multiple aetiologies influenced by a wide number of genetic, biological, psychosocial and environmental factors (e.g. multiple pregnancy, infection, placental abruption and stress) yet the chronology and aetiology of sPTB is insufficiently understood. Early sPTB is likely result from a complex interaction of maternal and/or fetal inflammatory responses which culminate in progressive cervical shortening and myometrial contractions.

A short cervix (detectable on transvaginal ultrasonography) has emerged as a useful predictor of sPTB in both low-risk and high-risk pregnancies. Risk of preterm birth is inversely related to cervical length; the shorter it is, the higher the risk of preterm birth. There may also be a number of other biomarkers [for example cervicovaginal fetal fibronectin (fFN) which can identify those women at the highest risk]. In clinical practice, once a woman has been identified as being at higher risk of sPTB by virtue of a short cervix, a decision regarding prophylactic treatment must be made. Three interventions have been proposed to treat patients with a short cervix; cervical cerclage, vaginal progesterone therapy and cervical pessary.

#### 1.1.1 Cervical cerclage

This is the insertion of a 'purse string' suture around the cervix under regional anaesthesia. There is little consensus on the optimal procedure or technique (e.g. low/high vaginal, abdominal, tape/nylon, single/multiple, endocervical/purse string) or timing of insertion (elective, ultrasound indicated, pre conceptual). Furthermore, the mechanism of action is not understood; cerclage may offer a degree of structural support, but also plays a role in maintaining a biochemical barrier protecting membranes against exposure to ascending pathogens. It also is known to induce an inflammatory response which may encourage tissue repair. A 'history indicated' cerclage is inserted in early pregnancy (8-14 weeks) in women who have a history of late miscarriage or preterm birth. The largest randomised controlled trial comparing history-indicated cerclage with expectant management (n=1292), demonstrated that benefit of cerclage was only seen in women with three prior fetal losses/premature deliveries, where their risk of preterm birth reduced by more than half.

Ultrasound indicated cerclage involves the insertion of cerclage as a therapeutic measure following evidence of cervical length shortening (a predictor of preterm birth). Benefit of this cerclage has been reported in a subgroup of high risk women (history of preterm second-trimester loss or birth before 36 weeks of gestation) who have a cervix <25 mm in length, with meta-analysis demonstrating a significant reduction in delivery before 35 weeks of gestation (relative risk [RR] 0.57; 95% CI 0.33–0.99 and RR 0.61; 95% CI 0.40–0.92) when compared with expectant management.

#### 1.1.2 Vaginal progesterone therapy

Physiologically, progesterone is responsible for maintaining myometrial quiescence during pregnancy and suppressing maternal immune system. As a result it has been advocated in the prevention of pre-term birth in singleton pregnancies. A Cochrane systematic review revealed that prophylactic progesterone (intramuscular and vaginal administration of varying doses) was associated with a significant reduction in preterm birth <34 weeks (one study; 142 women; risk ratio (RR) 0.15; 95% confidence interval (CI) 0.04–0.64) and preterm birth at less than 37 weeks (four studies; 1255 women; RR 0.80; 95% CI 0.70–0.92). A metaanalysis of vaginal progesterone treatment in all women with a short cervix <25mm showed a reduction preterm birth (<33 weeks (RR, 0.58; 95% confidence interval [CI], 0.42 to 0.80), <35 weeks (RR, 0.69; 95% CI, 0.55 to 0.88), and <28 weeks (RR, 0.50; 95% CI, 0.30 to 0.81) and neonatal composite morbidity and mortality (RR 0.57; 95% CI, 0.40 – 0.81). The plasma (and/or uterine) concentration of progesterone required to reduce sPTB is unknown, and the mechanism of action uncertain. It is, however, frequently used in clinical practice (usual dose 200-400 mg).

[figure not shown]

The doses of vaginal progesterone used in completed trials are 100 mg (n=142) or 200 mg (n=250). Whilst vaginal progesterone use for the prevention of sPTB is unlicensed, it is commonly used in clinical practice in the UK and Europe and is also recommended for use in clinical practice in the USA by the Society for Maternal and Fetal Medicine. The Royal College of Obstetricians and Gynaecologists (RCOG) recommend vaginal progesterone use in the context of clinical trials to determine whether its use is associated with improved fetal, neonatal and/or infant outcome.

### 1.1.3 Cervical pessary

The Arabin pessary is a round and cone shaped flexible silicon device which is designed to be inserted into the vagina and sit in the upper vaginal fornix, to support and incline the cervix, with the intention to prevent premature cervical shortening and preterm birth. Goya *et al* reported a multicentre randomised controlled trial (n=385) on pessary use in unselected women screened by TVS and showed that in women with a short cervical length (< 25 mm) between 18 and 22 weeks, the pessary reduced the rate of sPTB <34 weeks' gestation compared with controls (6% vs 27%, odds ratio 0.18, 95% CI 0.08 to 0.37; p<0.0001), with a significant difference detected in the occurrence of composite poor neonatal outcome. In a subsequent smaller RCT, 108 Asian women with a singleton pregnancy and a cervical length<25 mm at routine second-trimester TVS were randomized to a pessary and a control group. The mean gestational age at delivery was 38.1 weeks in the pessary group compared with 37.8 weeks in the expectant management group, with no significant differences in the rates of delivery before 28, 34 or 37 weeks.

## 1.2 Prediction of premature birth using biomarkers

### 1.2.1 Fetal fibronectin

Risk assessment and management of prematurity has been enhanced in recent years by the knowledge of pathophysiologically relevant biomarkers. fFN is an extracellular glycoprotein found in the decidua basalis in the pregnant uterus. Here it is concentrated between the decidua and the trophoblast and is best described as the 'glue' between the pregnancy and the uterus. In normal conditions fFN remains in this area, and very low concentrations are found in the cervico-vaginal secretions after 22 weeks. Higher concentrations at or after 22 weeks, or even as early as 13 weeks, detected by swab test in the cervicovaginal secretions have been associated with increased risk of sPTB. The use of fFN for distinguishing preterm contractions from preterm labour (PTL) in symptomatic patients is now well accepted, but for screening asymptomatic patients deemed to be at high risk of sPTB its role has been less clear due to the limited sensitivity and positive predictive value of the standard qualitative test which provides a positive or negative result based on a threshold of 50 ng/ml. Goldenberg *et al* (1996) showed that the specificity of fFN was consistently 96-98%, which is valuable because it means women with a negative test can be safely discharged, but a sensitivity of 0.63 means an fFN test at 22-24 weeks predicts only just over half of sPTB at <28 weeks. Studies using a quantitative assay (ELISA) demonstrate that the cervicovaginal fluid (CVF) quantitative fFN (qfFN) concentration correlates with the risk of sPTB and improved prediction has been demonstrated using thresholds both below and above 50 ng/ml (Abbott *et al*, In Press).

### 1.2.2 Natural antimicrobial peptides

More recently discovered biomarkers may represent alternative pathophysiological pathways and contribute to earlier risk prediction, with potential to increase the accuracy of existing tests. Our group has shown that the antimicrobial peptide (AMP) elafin (peptidase inhibitor 3 or skin-derived antiproteinase SKALP/Trappin-2) is a promising early predictive marker of cervical shortening and sPTB. This recent 'discovery' stage study determined that CVF elafin protein expression longitudinally in CVF from women at high risk of sPTB (previous history of late miscarriage or sPTB). The study demonstrated that in N=74 high risk women, CVF concentrations of elafin were significantly higher in women who developed a short cervix group (cases) compared to high risk women without cervical shortening (controls), regardless of gestation and treatment (ratio 2.71, CI 1.94 to 3.79, p<0.0005). Elafin concentrations predicted cervical shortening from 14 weeks' of pregnancy (n=11, ROC area = 1.00, p=0.0082) and remained three fold higher when cervical shortening was first detected (ratio 3.03 CI 1.92-4.81, p<0.0005). Elafin was unaltered by treatment (insertion of a cerclage or vaginal progesterone daily; ratio 1.28, CI: 0.88-1.87, p=0.196).

[figure not shown]

### 1.2.3 Salivary progesterone

A prospective study involving 90 high risk asymptomatic women in India showed that the mean value of salivary progesterone was significantly lower in all women who delivered at <37 weeks of gestation ( $n=38$ ), compared with the term group ( $n=52$ ;  $P < 0.001$ ). Our research group have previously demonstrated a suppression of the normal gestational rise in salivary progesterone (24-34 weeks') in high risk women who delivered before 34 weeks' gestation ( $n=12$ ), compared with those delivering spontaneously between 34 and 37 weeks' ( $n=28$ ), and those delivering at term ( $n=64$ ) ( $p=0.007$  versus 34-37 weeks', and  $p=0.009$  versus term deliveries). Analysis of progesterone concentrations in the saliva of >1000 high risk women is currently underway (The Poppy study).

### 1.3 Rationale for study

There have been no direct comparison of all three of these interventions and as such, there are no guidelines as to the optimal management of high-risk women who develop a sonographic short cervix. Women at high risk of sPTB who develop a short cervix cannot, at present, be counselled about which is the most suitable intervention to reduce their risk of delivering prematurely. Currently, cervical cerclage is the Royal College of Obstetricians (RCOG) recommended treatment for women with a short cervix <25mm and a history of 1 or more late miscarriages or preterm birth.

Our research group recently published an exploratory observational study to evaluate the relationship between proinflammatory cytokines, cervical shortening and intervention, within which 37 women who developed a short cervix were randomised to treatment with vaginal progesterone ( $n=17$ ) or cervical cerclage ( $n=19$ ). A clinically important trend towards benefit (gestation at delivery) was noted in the cerclage group [mean gestation 33.7 weeks' cerclage versus 31.5 weeks' progesterone] although this result did not achieve statistical significance.

Alfirevic *et al* compared retrospectively three separate cohorts of women with previous sPTB <34 weeks and short cervix treated with cerclage ( $n=142$ ), vaginal progesterone ( $n=59$ ) or a pessary ( $n=42$ ). There were no significant differences in rates of perinatal loss, neonatal morbidity or sPTB, apart from a higher rate of sPTB before 34 weeks' gestation in the vaginal progesterone vs pessary groups. It was concluded that randomized comparisons of these three management strategies, or combinations thereof, are needed to determine the optimal management of these women. If a randomised study, such as the one proposed, showed that the three treatments were equally efficacious, then women and clinicians would have greater choice regarding treatment plans, expensive surgery (and potential complications) could be avoided. The pessary could be inserted at a later gestational age, when cerclage is no longer performed, potentially in an outpatient setting.

This randomised controlled trial will answer the current clinical dilemma of which is the most effective method to treat women at high risk of sPTB who develop a short cervix.

### 1.4 Rationale for pre-intervention predictive biomarker testing in parallel

Whilst sPTB culminates in a common pathway of myometrial activation, cervical dilation and rupture of membranes, it is initiated by a number of different factors, which hinders accurate identification of at risk women and application of a 'one size fits all' preventative intervention. It is anticipated that the multiple pathways and pathologies preceding cervical shortening and sPTB, and thus a woman's response to various preventative interventions, may be differentiated by the expression of different biomarkers. We predict that the observed intervention effects may be enhanced by selection of sub-groups of women according to their biomarker expression i.e. that the underlying pathophysiology may determine the success of one intervention over the other. 'Pre-intervention' samples of blood, saliva and CVF will be taken from all women when randomised, and two weekly thereafter until 24 weeks' (or delivery). Biomarkers measured will include fFN, natural antimicrobial peptides and other inflammation related markers and salivary progesterone, whilst creating a biobank of samples for future analysis of other potential candidate biomarkers. We will also analyse blood biomarkers and DNA extracted from whole blood for genetic differences (e.g. SNP polymorphisms) in women destined to deliver prematurely during pregnancy compared to those who deliver at term. Bacterial and viral DNA/RNA extracted from vaginal swabs to determine the relationship between candidate biomarkers the vaginal microbiome and response to intervention. ≥

[figure not shown]

## **2 Trial Aim, Objectives, Design and Statistics**

### **2.1 Aim**

In a randomised controlled trial, to compare three evidence-based treatments for a short cervix detected by ultrasound scan in women at high risk of premature birth: cervical cerclage, cervical pessary and vaginal progesterone therapy.

### **2.2 Objectives**

The primary objectives of this study are:

- To determine if treatment with cervical cerclage, cervical pessary or vaginal progesterone in women at high risk of preterm birth who develop a short cervix by ultrasound measurement are equally efficacious to improve obstetric outcome by lengthening pregnancy and reducing the incidence of preterm delivery before 34 weeks' gestation.
- To evaluate the impact of the interventions on short term neonatal outcomes, assessed as a composite of perinatal death (within 28 days) and major morbidity

The secondary objectives are:

- To undertake an exploratory analysis to determine whether the response to intervention for a short cervix is related to the pre-intervention biomarker status (CVF, blood, saliva)
- To evaluate the acceptability to women and clinicians of each of the three treatment arms
- To assess the impact of both management strategies on health economic outcomes for mother and infant in terms of number of nights in each hospital setting; cost data to hospital discharge/28 days post natal (it is anticipated that a 6 month and 2 year follow up may be performed if funding is obtained).

### **2.3 Trial Design**

An open label, multi-centre three armed randomised controlled trial. Women who develop a short cervix will be randomised to one of 3 treatments: cervical cerclage (procedure to take place within 7 days of diagnosis, removed at 37 weeks'), cervical pessary (inserted at diagnosis and removed at 37 weeks'), vaginal progesterone (200 mg once daily per vagina until 34 weeks' gestation from time of randomisation). At an appropriate time-point between time of randomisation and time of intervention, women will provide a saliva sample, CVF sample and blood sample (for biomarker analysis, optional, if facilities allow). These will be repeated every approximately every two weeks according to routine clinic visits thereafter until 28 weeks' gestation.

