#### 3.4.1 Cervical cerclage

The cerclage procedure will be booked at the time of recruitment. It will be performed (according to local practice and procedures) within 7 days of recruitment to the trial. A vaginal cerclage will be inserted in the operating theatre by a clinician trained in the procedure, according to the technique preferred by the clinician. It is usually inserted under regional anaesthetic. Tocolysis, antibiotics and antenatal corticosteroids can be considered at the clinician's preference, but will be documented and considered in the analysis. The patient will usually go home the same day and will be followed up with two to four weekly transvaginal ultrasound scans (or more frequent if clinically indicated) according to local protocols. The suture is removed easily by exposing the cervix and cutting the knot, usually without the need for anaesthetic. This is done electively when a woman is 37 weeks' gestation, or if she presents in symptomatic preterm labour before labour becomes established, to avoid cervical trauma. The suture should also be removed if there is clinical evidence of chorioamnionitis. Cervical cerclage insertion is an established surgical procedure, which is associated with minimal risks. These include infection, miscarriage, bleeding, difficulty with suture removal and preterm prelabour rupture of membranes.

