#### 3.4.2 Vaginal progesterone

No significant adverse events have been reported with 200 mg vaginal progesterone. Vaginal progesterone once daily will be prescribed at the time of recruitment. Patients will be informed to insert vaginal progesterone every day until 34 weeks' gestation (or delivery, whichever is soonest). The patient will usually be followed up with two to four weekly transvaginal ultrasound scans (or more frequently if clinically indicated) according to local protocols. If the cervix shortens and membranes are visible, prior to 24 weeks' gestation, a rescue cerclage will be inserted, according to local protocols. Vaginal progesterone will be stored as per manufacturers instructions and dispensed by the hospital pharmacy. Licensed indications are for adjunctive use with oestrogen in post-menopausal women with an intact uterus (HRT). Progesterone will not be used within its licensed indications for this study. Any preparation of vaginal progesterone (200 mg) currently used in clinical practice for the prevention of preterm birth, will be allowed for use in the trial (eg Cyclogest, Uterogestan) according to individual site clinical protocols.

Contraindications are:

- known allergy or hypersensitivity to progesterone.
- severe hepatic dysfunction,
- undiagnosed vaginal bleeding,
- mammary or genital tract carcinoma,
- thrombophlebitis,
- thromboembolic disorders, • cerebral haemorrhage,
- porphyria.

[figure not shown]

If unexplained, sudden or gradual, partial or complete loss of vision, proptosis or diplopia, papilloedema, retinal vascular lesions or migraine occurs during therapy, the drug should be discontinued and appropriate diagnostic and therapeutic measures instituted. Vaginal progesterone 200mg should be used cautiously in patients with conditions that might be aggravated by fluid retention (e.g. hypertension, cardiac disease, renal disease, epilepsy, migraine, asthma); in patients with a history of depression, diabetes, mild to moderate hepatic dysfunction, migraine or photosensitivity and in breast-feeding mothers. Any adverse events experienced should be recorded as per the AE/ SAE section 8 of this protocol.

Indications for stopping treatment are:

- Elective (preterm) delivery
- Fetal membrane rupture
- Symptomatic placenta praevia
- Sudden or gradual, partial or complete loss of vision,
- Proptosis or diplopia
- Papilloedema
- Other patient reaction or sensitivity to progesterone
- Patient request

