### **3.5 Pre- and Post intervention biomarker measurement**

At a convenient time between randomisation and intervention, the following procedures will take place in order to obtain biomarker levels (if study site facilities allow and the participant has consented to them):

[figure not shown]

- a) One sterile speculum examination and approximately 4 cervico-vaginal swabs (high vaginal and/or endocervical). The speculum examination will last approximately 20-30 seconds (normally 15 seconds if only 1 swab is taken as per routine clinical care after 18 weeks'). qfFN will be performed from 18 weeks' gestation.
- b) A saliva sample (5 ml) will be obtained.
- c) Two blood samples will be taken (2 x 15 ml/1 tablespoon), one for genetic analysis; one for biomarker analysis.

CVF sampling will be repeated, if facilities allow, at each subsequent routine clinic visit until 28 weeks' gestation. Sample collection is not mandatory for trial participation. Some women may only want to provide samples at a single visit or only provide one or more of the samples listed.

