| Transvaginal ultrasound Scan                                          | C                                                                               |                                                                            | C                                                 | O                                          |                                                                    |                                              |
| Biological sample collection                                          | O                                                                               |                                                                            | O                                                 | O                                          |                                                                    |                                              |
| Adverse events (AEs) and changes to interventions                     |                                                                                 |                                                                            | C                                                 | O                                          | C                                                                  | C                                            |
| Count un-used medication if appropriate                               |                                                                                 |                                                                            |                                                   |                                            | C                                                                  |                                              |
| Pessary/Cerclage removal booked/performed at 37 weeks' if appropriate |                                                                                 |                                                                            |                                                   |                                            | C                                                                  |                                              |

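### The optional baseline biomarker samples are placed after open allocation, in a window whose length differs by arm; they should be taken after consent and before the allocation is released

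*Protocol*

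**What the plan says.** Protocol section 2.2 lists an exploratory secondary objective: to find out "whether the response to intervention for a short cervix is related to the pre-intervention biomarker status". Four places give the time of the first sample:

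- Section 1.4: "samples of blood, saliva and CVF will be taken from all women when randomised".
- Section 2.3: "At an appropriate time-point between time of randomisation and time of intervention, women will provide a saliva sample, CVF sample and blood sample".
- Section 3.5: "At a convenient time between randomisation and intervention, the following procedures will take place in order to obtain biomarker levels".
- Schedule of Visits: the row "Biological sample collection" is marked optional in the screening and randomisation column (window −7 to 0 days) and is blank for the intervention day.

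Sampling is optional (sections 2.3, 3.1 and 3.5). The trial is open label and each woman learns her arm at recruitment (section 3.3).

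Treatment starts at different times by arm. For progesterone, section 2.3 counts from randomisation and section 3.4.2 says "Vaginal progesterone once daily will be prescribed at the time of recruitment". Cerclage is done "within 7 days of recruitment to the trial" (section 3.4.1). The pessary goes in at diagnosis according to section 2.3, but up to 7 days after recruitment according to section 3.4.3.

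On quantitative fetal fibronectin, section 3.5 says: "qfFN will be performed from 18 weeks' gestation". Randomisation runs from 14+0 to 23+6 weeks (section 3.3).

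**The concern.** To ask whether response to treatment depends on a baseline marker, the marker must be collected in the same way in every arm. Sampling before allocation guarantees this; sampling after open allocation does not, for two reasons.

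- **Uptake.** The sample is optional and the woman already knows her arm. Who gives one may differ by arm, so the sampled women may no longer be comparable between arms.
- **Timing.** One form of words is applied to windows of unequal length. A sample may be taken on the day of randomisation in one arm and some days later in another, in women whose cervix may be changing.

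Either could produce a marker-by-treatment difference that has nothing to do with the treatments. Salivary progesterone is the most exposed marker, because a sample given after the first progesterone dose would reflect the treatment. Such a sample would breach the written rule, but the protocol does not say how it would be classed. An analysis plan can describe or exclude mistimed and missing samples, but it cannot recover them.

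**Working it through.** The protocol gives no figure for this point, so there is none to reproduce. The check sets the timing statements side by side and counts days.

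**1. When is the sample taken?** Section 1.4 says at randomisation, in all women. Sections 2.3 and 3.5 allow any suitable time after randomisation and before treatment. The schedule's column covers both screening and randomisation, so it would accommodate a sample before allocation but does not require one. These statements do not give one sampling time.

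**2. How long is the window between randomisation and treatment?** Recruitment and randomisation are taken as the same day, as in section 3.3.

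| Arm | Source | Window (days) |
|---|---|---|
| Progesterone | 2.3, 3.4.2 | about 0 |
| Cerclage | 3.4.1 | 0 to 7 |
| Pessary | 2.3 | 0 |
| Pessary | 3.4.3 | 0 to 7 |

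The largest possible difference in sampling delay between cerclage and progesterone is 7 − 0 = 7 days. The pessary matches progesterone under section 2.3 and cerclage under section 3.4.3. On either reading the three windows are not all equal. The 7 days limit the procedure, not the sample, so this is the most that the wording permits, not an expected delay.

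**3. Can uptake depend on the arm?** Yes in principle: disclosure at recruitment (3.3) comes before the sample (2.3, 3.5), which may be declined in whole or in part (3.5). The protocol gives no figure from which to estimate the size of any imbalance.

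**4. What does the 18-week start of qfFN remove?** In days of gestation, 14+0 is 98, 17+6 is 125 and 23+6 is 167.

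- Eligible days: 167 − 98 + 1 = 70.
- Days before 18+0: 125 − 98 + 1 = 28.
- Share of days: 28/70 = 40%.

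The protocol does not give the distribution of gestation at entry, so the share of women is an assumption. With 540 women (180 per arm) and full sampling:

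| Assumed share entering before 18+0 | Women without baseline qfFN | Left per arm |
|---|---|---|
| 10% | 54 | 162 |
| 20% | 108 | 144 |
| 30% | 162 | 126 |
| 40% | 216 | 108 |

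There is one exception at the boundary. A woman randomised at 17+0 to 17+6 could reach 18+0 before a procedure up to 7 days later, but not before progesterone started at randomisation. Defining the qfFN analysis by gestation at randomisation removes this.

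**The case against.** The strongest reply is that the sampling rule is the same for all arms and precedes treatment, which is exactly the status that the objective names. Knowing her arm does not change the concentration of a marker in a woman's cervicovaginal fluid, saliva or blood. No section sets a sampling time by arm, and nothing suggests that samples are held back to day 7. Section 3.1 treats consent to sampling as a matter of trial entry, so most decisions may be made before allocation. Site facilities are another stated reason for missing samples, unrelated to the woman's choice. All of this stands, and it makes the risk small. It does not remove the risk, because section 3.5 still lets a woman give only some of the samples after she knows her arm, and the windows still differ.

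A reader might infer that the trial has no valid or comparable baseline for this objective. The protocol does not support that: a sample that follows the rule is a pre-treatment sample. A reader might also infer that the 18-week rule makes the arms non-comparable. It does not. Apart from the boundary week, whether a woman can have a baseline qfFN depends on her gestation at entry. Gestation is a minimisation variable (section 3.3), and the other markers are untouched.

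It can also be said that swabs before allocation might need a second speculum examination, since the eligibility examination may come before consent. That is possible. But section 3.5 already provides for a speculum examination for sampling, so the change moves that examination and does not add one to the plan. Finally, how to class late samples and define the qfFN analysis set may properly be left to the SAP. The time of collection cannot.

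**Conclusion.** The point holds as a low-cost improvement. The protocol is inconsistent about when the baseline sample is taken. Two of its four statements place an optional sample after open allocation, in a window of about 0 days for progesterone, up to 7 days for cerclage, and 0 or up to 7 days for the pessary. Uptake and timing can therefore depend on the arm and could bias the marker-by-treatment analysis. The size of any bias cannot be estimated from the protocol. The conclusion assumes that sites use the latitude that sections 2.3 and 3.5 give; if every site sampled at randomisation, as section 1.4 says, the timing difference would vanish and only arm-related uptake would remain.

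The qfFN gap is a separate limit on scope, not a bias between arms: 40% of eligible days, with the share of women unknown.

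The impact is low. The objective is secondary and exploratory, and neither the primary endpoint nor the equivalence comparison is affected.

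**What to change.** - Reconcile sections 1.4, 2.3 and 3.5 and the Schedule of Visits so that baseline cervicovaginal fluid, saliva and blood are taken after consent and before the allocation is released.
- State, here or in the SAP, that any sample taken after treatment has started counts as post-intervention and is not used as a baseline.
- Reconcile the pessary timing in sections 2.3 and 3.4.3. Which timing applies is for the investigators to decide.
- State that the qfFN part of the objective covers women randomised from 18+0, and that no later qfFN stands in for a baseline.

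The cost is protocol wording and a site instruction, with no extra visit or sample. The downsides are a short delay before randomisation, a few samples from women who are not then randomised, and a smaller stated population for the qfFN analysis.
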